## Abstract

**Background:**

Young children’s healthy development depends on nurturing care, which ensures health, nutrition, responsive caregiving, safety and security, and early learning. Infancy and childhood are characterized by rapid growth and development, and these two factors contribute largely to determining health status and well-being across the lifespan. Identification of modifiable risk factors and prognostic factors during the critical periods of life will contribute to the development of effective prevention and intervention strategies.

The NASCITA (*NAscere e creSCere in ITAlia*) study was created to evaluate physical, cognitive, and psychological development, health status and health resource utilization during the first six years of life in a cohort of newborns, and to evaluate potential associated factors.

**Methods:**

NASCITA is an ongoing, dynamic, prospective, population-based birth cohort study of an expected number of more than 5000 newborns who will be recruited in 22 national geographic clusters starting in 2019. It was designed to follow children from birth to school entry age for a wide range of determinants, disorders, and diseases. Recruitment of the newborns (and their parents) will take place during the first routine well-child visit, which takes place at the office of the pediatrician assigned to them by the local health unit of residence, and which is scheduled for all newborns born in Italy within the first 45 days of their life.

Data will be web-based and collected by the family pediatricians during each of the 7 standard well-child visits scheduled for all children during their first 6 years of life. Information on every contact with the enrolled children in addition to these prescheduled visits will be also recorded.

**Discussion:**

The NASCITA cohort study provides a framework in which children are followed from birth to six-years of age. NASCITA will broaden our understanding of the contribution of early-life factors to infant and child health and development. NASCITA provides opportunities to initiate new studies, also experimental ones, in parts of the cohort, and will contribute relevant information on determinants and health outcomes to policy and decision makers. Cohort details can be found on https://coortenascita.marionegri.it.

**Trial registration:**

Clinicaltrials.gov: NCT03894566.

**Ethics committee approval**: 6 February 2019, Verbale N 59.

## Background

As concisely and effectively reported in an excellent series of papers on early child development: *Childhood development is a maturational process resulting in an ordered progression of perceptual, motor, cognitive, language, socio-emotional, and self-regulation skills. The acquisition of skills throughout the life-cycle therefore builds on the foundational capacities established in early childhood.*^1^ Multiple factors influence the acquisition of competencies and skills, including health, nutrition, security and safety, responsive caregiving, and early learning. All are necessary for nurturing care [1, 2]. Nurturing care reduces the detrimental effects of disadvantage on brain structure and function which, in turn, improves children’s health, growth, and development [1, 3]. Nurturing care is characterized by a home environment that is sensitive to children’s health and nutritional needs, responsive, emotionally supportive, and developmentally stimulating and appropriate, with opportunities for play and exploration and protection from adversities [1, 4]. Nurturing care extends beyond families to include community care givers for families [1–5]. The environmental, social, economic, political, climatic, and cultural contexts can therefore affect nurturing care and early childhood development.

Infancy and childhood are characterized by rapid growth and development, and are considered critical periods of development in life that strongly contribute to health status, well-being, and behavior across the lifespan [2]. In fact, many common diseases and challenges in adult life can be traced back to early childhood [1, 6].

The heterogeneity of the population in Italy is increasing, and sociodemographic and geographic differentials (e.g., in education and migrant status) have been associated with health disparities [7, 8]. In order to adequately describe public health in Italy, epidemiological studies enrolling participants from all population groups and settings are therefore needed.

Although Italy has a public, universal healthcare system that should pose no legal or financial barriers to subgroups of the population, considerable health inequalities exist [9]. Differences arise from differences in factors such as health behavior, exposure, environment, genes, etc.

Life course approaches show that a considerable part of these inequalities is determined by exposure, health status, and development in utero and in early childhood [1, 6]. Moreover, in early childhood, children are particularly vulnerable to the influence of different factors and their interactions. While this fact is well documented, underlying mechanisms remain unclear. It is still poorly understood how specific social factors, socioeconomic status, living conditions, parental and stakeholder care, and attitudes act on the well-being of children or in creating health inequalities among children. Moreover, interactions between these factors need to be investigated [10–12].

Birth cohort studies are a powerful study design for medical and social research because they are designed to observe the impact of early exposures prospectively and at multiple time points during child development [13]. A number of birth cohort studies have been carried out [14], also in Italy [15, 16], with different aims and sizes. The overall aim of the NASCITA study (*NAscere e creSCere in ITAlia*) is to improve the understanding of the health status of Italian children early on and how it is affected by social and health determinants. Like many other cohorts, it will address multiple research questions [15, 16]. The findings will add important evidence, in terms of epidemiological data, for the development of specific prevention measures and interventions to improve the health status of children, in particular more vulnerable ones.

### Hypothesis and significance

We hypothesize that:

- differences due to environmental, sociodemographic, and parental determinants, as well as to child characteristics and physician attitudes, exist between geographic areas in a population’s health and in the use of health resources in the first few years of life;

- differences exist in the appropriateness of care provided by the National Health Service at different levels (regional, local, family pediatrician);

- differences exist between geographical settings in parental attitudes toward the recommendations concerning children’s health care and these differences may be a determinant of child development and well-being and health resource utilization;

- the existing differences between geographical settings in the opportunities for children to access educational/socialization experiences (e.g. day-care centers) may have an impact on development.

### Aims

The main aim of the NASCITA cohort is to evaluate physical, cognitive, and psychological development, and health status and health resource use during the first six years of life in a group of newborns, and to evaluate potential associated factors. The specific research questions are:
the relationship between child development and the domains that affect nurturing care during the preschool period: health (disease prevention and treatment), nutrition (breastfeeding and dietary approach), safety and security (care and early intervention for vulnerable children), responsive caregiving (caregiving routine), and early learning (home opportunities to explore and learn);the association between the well-being of children and parental adherence to the recommendations for better child care and development;the potential factors influencing child well-being and growth and development, including the acquisition of competences;the differences between geographical settings in educational and socialization opportunities available for young children and in the care provided by the family pediatricians and by the National Health Service for the same needs;

## Methods

### Study area and setting

Italy is located in southern Europe and comprises the long, boot-shaped Italian peninsula, the southern side of Alps, the large plain of the Po Valley and some islands including Sicily and Sardinia. Almost 40% of the Italian territory is mountainous, and there is a coastline of 7600 km on the Adriatic Sea, Ionian Sea, Tyrrhenian Sea, Ligurian Sea, Sea of Sardinia and Strait of Sicily. Italy is subdivided into 20 regions and is further divided into 14 metropolitan cities and 96 provinces, which in turn are subdivided into 7960 municipalities. A gaping North–South divide is a major factor of socio-economic weakness and can be noted by the huge difference in statistical income between the northern and southern regions and municipalities [17]. Twenty-two geographic clusters were identified as representative of the country based on geographic and socio-economic characteristics and administrative divisions, using the National Statistics Institute definitions for each town/city [18]. See Fig. 1 for the geographical distribution of the NASCITA cohort. Pediatricians and newborns of all the 22 identified clusters will be involved in the study.

**Fig. 1 Fig1:**
[figure not shown]
Geographical distribution of the NASCITA cohort

Italian healthcare is provided free or at a nominal charge through a network of Local Health Units (LHU). Each LHU consists of a number of healthcare districts, which are population-based territorial entities that aggregate different municipalities. Every Italian resident is registered with a family (pediatric or general) practitioner. Children are assigned to a pediatrician until they are 6 years old; afterwards, the parents can choose to register a child with a general practitioner. All adolescents > 13 years old are assigned to a general practitioner. In Italy there are about 7500 family pediatricians, for an average of 450.000 births/year [9]. About 60 newborns/year are therefore assigned to each pediatrician. All children are scheduled 7 well-child visits during their first 6 years of life (within 45 days of life and at 3, 6, 12, 24, 36, and 72 months of age). This list includes the recommended age for each well-child visit by the family pediatrician to ensure necessary preventive care, monitor a child’s growth and development, and establish a relationship between the child and his/her parents and the pediatrician.

### Study design

NASCITA is an ongoing, dynamic, prospective, population-based birth cohort study. From the start of 2019, newborns will be continuously included in the study for (at least) an entire one-year period chosen by each participating family pediatrician and will be followed prospectively until at least the age of 6 years. Given the ongoing character of the study, no maximum number of inclusions has been set. Cohort details can also be found on https://coortenascita.marionegri.it.

### Participant characteristics

The study population of the NASCITA cohort study will consist of all Italian children born during (at least) a one-year period who will be followed by participating pediatricians until the age of 6 years and whose parents agree to participate. Data on all newborns, including those with, e.g., congenital malformations, will be collected. We consider it valuable to have these data, also to be able to describe the epidemiological data more fully. The characteristics of this population will be evaluated separately in the analyses.

### Inclusion and exclusion criteria

The only inclusion criterion for participating in NASCITA is to be born in Italy during the period chosen by each pediatrician participating in the cohort study. Children whose parents do not agree to participate, or decide to withdraw, will be excluded from the study.

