With the parents’ consent, data on children withdrawing after 12 months of age will be considered in the analysis for the relevant time period of participation (e.g. rate of exclusive breastfeeding, reading out loud, SIDS prevention, etc.). Data will be deleted upon parents’ request.

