### Analysis plan

The analysis plan for the NASCITA cohort entails the investigation of several exposures and outcomes in order to address numerous research questions.

The main independent variables that will be tested are:

Maternal/paternal age.

Education level.

Employment.

Marital status.

Parental health status.

Parental lifestyle habits (smoking, alcohol).

A few examples of the dependent variables are:

Vaccination in pregnancy.

Folic acid prophylaxis.

Birthweight.

Duration of breastfeeding.

Reading out loud.

Sleep position.

Overweight and obesity.

Neurocognitive development.

Prescription prevalence and appropriateness.

Nursery school attendance.

A few of these variables will be tested as both independent and dependent variables based on the kind of analyses (e.g., reading out loud will be the dependent variable while testing the influence of maternal age or educational level, but will be considered an independent variable when possible factors influencing children’s development are tested).

Examples of the NASCITA STUDY’S research questions are:

- the relationship between mothers’ age, education level, and geographic area (independent variables) and vaccination in pregnancy (Influenza and Tdap vaccines) (dependent variable);

- the association between maternal smoking in pregnancy (independent variable) and birthweight (dependent variable);

- the relationship between pregnancy, perinatal, and newborn growth characteristics and occurrence of adverse outcomes (i.e., obesity, hypertension, wheezing, eczema, hay fever, and asthma);

- the relationship between parents’ educational level (independent variable) and duration of breastfeeding (at discharge from hospital and at 3 and 6 months) (dependent variable);

- the relationship between parents’ educational level (independent variable) and children’s weight and BMI/percentage of overweight/obese status (dependent variable);

- the association between lifestyle factors and health inequalities and the trajectory of health in the preschool period;

- the association between geographical setting and nursery school attendance;

- the association between geographical setting and quality of care in terms of prevalence and appropriateness of drug prescriptions.

In all of the of the analyses, the effect of the geographic and environmental setting will be evaluated.

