### Ethics and dissemination

The study was approved by the Fondazione IRCCS Istituto Neurologico Carlo Besta’s Ethics Committee (6 February 2019, Verbale n.59). A consent form for participation will be signed by the pediatricians upon their first access to the web site. A paper consent form will be signed by parents at the first visit. This form includes the consent to data collection at each contact with the pediatrician during the six-year study period (first 6 years of the child’s life). The filled in consent form will be stored by the pediatrician for ten years. Withdrawal from the study is guaranteed at any time both to pediatricians and parents. When consent is withdrawn, the child’s data collected up to that point will be kept in the analyses, but no further data will be collected. Standard procedures for the protection of confidential individual information will be applied according to national and international ethical recommendations and guidelines as well as national legal regulations. Data will be pseudonymized and all analyses will be conducted with fully anonymized data sets.

A newsletter report will periodically be sent to the pediatricians and uploaded on the web site. During the study, different tools will be used to update the participating families. Ad-hoc information material will be created and will be disseminated to families through newsletters and the website. Collected data will be periodically analyzed according to the aims of the project, and findings reported to lay people and the scientific community.

The coordinating center will provide the information, but the pediatricians will also be able to provide the families with information deriving from the cohort during their visits.When the enrolled children reach the age of 6 years, if not decided otherwise in the meantime, their personal files will no longer updated, but will be kept for another 10 years in the database.

NASCITA proposes to be a resource for the research community, so data will be available to public researchers outside the NASCITA research group upon request for collaborative research initiatives, after approval by the scientific committee.

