### Strengths and limitations of this study

NASCITA is entirely embedded in the child health care practice foreseen by the National Health Service and provided by family pediatricians. Recruitment and follow-up coincide with routine contact moments, so broad participation and follow-up rates are expected. Collaboration with other cohorts is foreseen. The NASCITA cohort data will be linkable and integrable with other data sources, such as routinely collected health data or data from other projects, as part of scientific collaborations.

High participation rates would allow an appropriate description and evaluation of all the different national territorial clusters. Moreover, NASCITA will provide opportunities to initiate new, experimental studies in subgroups of the cohort, and will contribute relevant information on determinants and health outcomes to policy and decision makers.

Since loss to follow-up is always a cause for concern in cohort studies and should be minimized, efforts have been made to establish a close and trust-based relationship with all participants. These efforts involve the creation of ad-hoc information material, the website, and newsletters to keep in touch with the study participants and to apply health promotion measures within the cohort. The estimated 20% loss to follow-up would, in any case, lead to a sample size that is large enough to be able to study common childhood exposures and outcomes. With the parents’ consent, data on children withdrawing after 12 months of age will be considered in the analysis.

A limit of the NASCITA study (as with any observational study) is the possibility of selection bias in the study population. The pediatricians recruited represent a co-operative sample, not a random sample, and should not be considered to be representative of the population of family pediatricians. The pediatricians, for example, could be more sensitive to better care practices or recommendations, and could influence the parents accordingly, promoting, for example, reading out loud to children. The target population of the study, however, will be the newborns (and their families) who are assigned to the pediatricians by the LHU based on places that have been freed up with those pediatricians. No selection bias in the population should therefore occur.

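### The article gives conflicting rules for the data of withdrawn children, so it is unclear whether early withdrawers count in outcomes already recorded at birth, 3 and 6 months

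*Protocol article*

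**What the plan says.** Four places in the protocol article deal with withdrawal.

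- **Inclusion and exclusion criteria:** "Children whose parents do not agree to participate, or decide to withdraw, will be excluded from the study". No age limit is given, and data already collected are not mentioned.
- **Study population size:** subject to parental consent, "data on children withdrawing after 12 months of age will be considered in the analysis for the relevant time period of participation". The next sentence adds "Data will be deleted upon parents’ request".
- **Strengths and limitations of this study:** the same 12-month condition, again subject to parental consent: "data on children withdrawing after 12 months of age will be considered in the analysis". Deletion is not mentioned.
- **Ethics and dissemination:** "Withdrawal from the study is guaranteed at any time both to pediatricians and parents". Once consent is withdrawn, the child's "data collected up to that point will be kept in the analyses, but no further data will be collected". No age threshold, further consent step or deletion exception appears.

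The Analysis plan names outcomes that are complete well before 12 months, among them "the association between maternal smoking in pregnancy (independent variable) and birthweight (dependent variable") and "duration of breastfeeding (at discharge from hospital and at 3 and 6 months) (dependent variable").

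**The concern.** A rule for withdrawn participants decides who is in the denominator of every early outcome. Here the sections do not lead to the same dataset. Because withdrawal is allowed at any time, a child who leaves in the first year is a foreseeable case.

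Two things are at stake. First, the 12-month wording makes inclusion in an analysis of birthweight or 3-month breastfeeding depend on a decision the parents took later. If that decision is related to parental education, geography or the outcome itself, prevalences and associations can be distorted, although the records exist. Second, with more than one rule in print, an analyst could cite the article for more than one dataset, and the choice could be made after results are known. The deletion clause also bears on what families are told about their data.

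**Working it through.** **Passages side by side.** Take a child withdrawn at 8 months, after the visits within 45 days and at 3 and 6 months; a child withdrawn at 30 months; and parents who ask for deletion.

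| Section | Withdrawn at 8 months | Withdrawn at 30 months | Deletion requested |
|---|---|---|---|
| Inclusion and exclusion criteria | Child excluded; existing data not addressed | Same | Not addressed |
| Study population size | Not covered; left out by implication | Used for the period of participation, if parents consent | Deleted |
| Strengths and limitations | Not covered; left out by implication | Used, if parents consent | Not addressed |
| Ethics and dissemination | Kept | Kept, no further consent condition | Kept; no exception stated |

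The firm conflicts are in the 8-month column (kept, or by implication left out) and the deletion column (deleted, or kept). The extra consent condition at 30 months is a further mismatch. The eligibility sentence is ambiguous rather than clearly contradictory.

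**The plan's own figure.** Minimum enrolment is 5000 and the estimated loss is 20%: 5000 × (1 − 0.20) = 4000, as stated. The conflict does not depend on this figure.

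**Possible size of the bias.** Inputs from the article: 5000 children and exclusive breastfeeding until 6 months at 42.7% (Table 1). The article gives neither the share withdrawing before 12 months (w) nor the difference in prevalence between those who stay and those who withdraw early (d), so both are assumed.

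If prevalence is p_s in stayers and p_s − d in early withdrawers, the full-cohort value is p = (1 − w)·p_s + w·(p_s − d) = p_s − w·d. Dropping the early withdrawers therefore overstates prevalence by w × d.

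The 95% half-width is 1.96 × √(0.427 × 0.573 / n), with n = 5000 × (1 − w). With nobody dropped it is 1.37 points.

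| Early withdrawal w | Children dropped | Bias, d = 0 | Bias, d = 10 points | Bias, d = 20 points | 95% half-width |
|---|---|---|---|---|---|
| 1% | 50 | 0 | 0.1 | 0.2 | 1.38 |
| 5% | 250 | 0 | 0.5 | 1.0 | 1.41 |
| 10% | 500 | 0 | 1.0 | 2.0 | 1.45 |

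Bias and half-width are in percentage points. Within this range, only the most extreme combination exceeds sampling error. As w approaches zero, so does the bias.

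**The case against.** The strongest reply is that this is loose wording with little consequence. Several parts of that reply stand.

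- A reader might infer that the eligibility sentence orders withdrawn children's data to be discarded. It does not say so. It treats families who never agree and families who leave together, and can be read as saying only that participation ends, which would fit the ethics section.
- A reader might infer that the 12-month wording expressly discards earlier withdrawers. It does not. It says what happens after 12 months and is silent on the rest, so exclusion is by implication.
- A reader might apply the bias formula to the whole 20% loss: 20% × 20 points = 4.0 points. The documents do not support this. Study population size places that loss after the first two years, so the 12-month limit would not remove those children's early records, given parental consent. The 20% is also loss to follow-up, and the share that is formal withdrawal is not given.
- A reader might conclude that selection bias is established. That would need both a non-trivial early-withdrawal rate and withdrawal related to exposure or outcome. The article gives evidence of neither, and expects attrition in the first two years to be irrelevant.
- The 12-month limit may reflect the terms of the consent form, which is not shown.

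These points limit the size and certainty of the harm. They do not reconcile the ethics section with the 12-month wording, or the deletion clause with a statement that data are kept.

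**Conclusion.** The contradiction holds. Ethics and dissemination conflicts with Study population size and with Strengths and limitations over children who withdraw before 12 months. It also conflicts with Study population size over deletion. The eligibility sentence needs clarifying.

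The statistical consequence is a risk of selection bias in outcomes already recorded at birth, 3 and 6 months, and its size is unknown. Under the assumed 1–10% early withdrawal and 10–20 point difference it is about 0.1–2.0 points on a prevalence near 43%, against a half-width of about 1.4. It is zero if withdrawal is unrelated to the outcome, and near zero if early attrition is as low as the article expects. Effects on associations were not calculated.

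This should be fixed because the rule is contradictory and the correction is cheap. It has not been shown to distort the results materially.

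**What to change.** Adopt one rule in all four sections and check it against the consent form:

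1. Follow-up stops at withdrawal. Data collected up to that date are analysed whatever the child's age, unless the parents request deletion.
2. Report the number of children withdrawn, by age at withdrawal, and the number whose data were deleted.
3. In Inclusion and exclusion criteria, limit exclusion to children whose parents never consent.
4. In Study population size and in Strengths and limitations, remove the 12-month condition. In Ethics and dissemination, add the deletion exception.

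If the consent form does not allow retention of data for withdrawals before 12 months, state that limit identically in all four sections and report how many children it affects.

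The cost is wording in four places, a check of the consent form and a short count in each report. No new data are needed.
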